#### Primary outcome

The primary outcome measurement is the proportion of responders at week 16. A responder is defined as a participant with a decrease of at least 50% less headache days during 4 weeks. A participant with a reduction of less than 50% headache days, including anyone with missing data, is defined as a nonresponder. This outcome measurement will be assessed at week 16 after randomization.

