#### Secondary outcome

The secondary outcome measurements are (1) number of headache days per 4 weeks, (2) the mean intensity of headache recorded by visual analogue scale score and grade of headache intensity per 4 weeks, (3) the reduction of medication intake per 4 weeks, (4) the 36-item short form health survey (SF-36) [20], (5) Hamilton Depression Scale (HAMD) [21] and Hamilton Anxiety Scale (HAMA) [22] results, (6) number of participants with adverse events (AEs) and serious adverse events (SAEs), (7) expectation values of acupuncture treatment, (8) the intensity of the *deqi* sensation.

All participants will be asked to complete a daily headache dairy and return them to assessors by emails, short messages or telephone calls throughout the whole 36-week observation period. The first three secondary outcomes will be extracted from the headache diaries. And the three outcomes followed will be assessed at each visiting time point. All of the above outcome measurements will be assessed at baseline, and at 4, 8, 12, 16, 20, 24, 28, and 32 weeks after randomization. Moreover, the expectation value of acupuncture treatment will be collected at baseline and week 8 after randomization, and the intensity of the *deqi* sensation will be assessed at 5 minutes after each treatment using the Massachusetts General Hospital Acupuncture Sensation Scale (MASS).

Details of AEs and SAEs will be documented during the 36-week period, such as occurrence time, duration, coping methods, and the correlation with treatment. AEs include bleeding, hematoma, fainting, severe pain, local infection, and so on, while SAEs are defined as life-threatening events, leading to significant or persisted disability, resulting in or prolonging hospitalization.

Researchers responsible for recruiting participants and assessors responsible for collecting data must receive training to ensure all of them have the same standards and understand the purpose, contents, and quality control of the trial. Detailed time points of outcome assessments are provided in Fig. 2.

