### Statistical analysis

Primary analysis will be based on intention-to-treat population, including participants with at least one assessment of the primary outcome and one acupuncture session. Per protocol (PP) analysis will be performed to test the robustness of the primary analysis. PP population will include participants receiving at least 12 sessions of acupuncture and be assessed at week 8 and 16.

The primary outcome will be analyzed with a random intercept logistic regression model, taking treatment allocation as a random factor and taking sex, age, and duration of headache as fixed factors. The secondary outcomes (headache days, headache intensity, SF-36, HAMA, HAMD results) will be analyzed using a generalized least squares regression model, with the same covariates as the primary outcome. For the rest of outcomes, we will make pairwise comparisons using a general linear model adjusted for baseline value, age, sex, and disease course. Missing values of the primary outcome will be imputed by the last-observation-carried-forward method. We will run several sensitivity analysis to ensure the robustness of the imputation: first, lost-to-follow-up participants in the acupuncture group will be recognized as nonresponders, whereas those in the superficial acupuncture group will be recognized as responders; second, lost-to-follow-up participants will be counted as responders in the acupuncture group but nonresponders in the superficial group; Third, all lost-to-follow-up participants will be treated as nonresponders. Missing values in the secondary outcomes will be imputed by using the multiple imputation method (*n* = 5).

All confidence intervals will be two-sided 95% intervals comparing acupuncture to superficial acupuncture and all statistical hypotheses will be two-sided tests. Analyses will be performed using the R and Stata programs.

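### Missing week-16 responder status is carried forward while the headache-day count behind it is multiply imputed, so the primary and first secondary outcomes rest on inconsistent missing-data assumptions

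*Protocol article*

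**What the plan says.** All places are in the protocol article.

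- **Primary outcome:** "The primary outcome measurement is the proportion of responders at week 16". Response is a cut of the headache-day count: "A responder is defined as a participant with a decrease of at least 50% less headache days during 4 weeks". The same section adds a missing-data rule: a participant with too small a reduction, "including anyone with missing data, is defined as a nonresponder".
- **Secondary outcome:** the first item is the "number of headache days per 4 weeks". Its source is the diary: "The first three secondary outcomes will be extracted from the headache diaries". Week 16 is among its assessment times.
- **Statistical analysis:** "Missing values of the primary outcome will be imputed by the last-observation-carried-forward method". For the rest, "Missing values in the secondary outcomes will be imputed by using the multiple imputation method", with five imputations. Three sensitivity analyses for the primary outcome follow. Two are opposite extreme cases for those lost to follow-up, and the third counts all of them as nonresponders.
- **Study design:** treatment lasts 8 weeks and follow-up 24 weeks, with three sessions a week in weeks 1 to 4 and two a week in weeks 5 to 8.

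**The concern.** Responder status at week 16 is a function of the baseline and week-16 headache-day counts. If the week-16 count is missing, the plan predicts it from a model with uncertainty when it is analysed as days. When it is analysed as response, the plan holds the last status fixed and treats it as known.

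The last-observation rule suits this endpoint poorly. Week 16 lies 8 weeks after the last session, and the stated aim is the long-term effect. A status carried from week 4 or 8 was recorded on treatment. Using it at week 16 assumes that the response lasted, which is the question under study. The Discussion itself expects response to change over this period: it cites a review in which the placebo effect rose to 12 weeks and fell afterwards.

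At stake are some bias of unknown sign in the primary estimate, a standard error that leaves out imputation uncertainty, and a primary and a secondary result on the same diary data that rest on different assumptions.

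**Working it through.** The plan gives no figure for the effect of missing data, so there is none to reproduce. Inputs from Study population and sample size are responder proportions of 46% and 35%, 10% attrition and 109 per arm. Every other input below is an assumption.

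**1. Who is affected.** Weeks 4 and 8 are on-treatment assessments; week 12 onward is post-treatment. Session 12 falls at the end of week 4 (3 × 4 = 12). Participants removed under Dropout criteria for not reaching 12 sessions will therefore often have only on-treatment data to carry. Someone last seen at week 12 carries a post-treatment status.

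**2. Shift in the difference from carrying forward.** Let m be the share missing in an arm, and d the amount by which carried response exceeds true week-16 response among those missing. Then

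shift = m(acupuncture) × d(acupuncture) − m(control) × d(control).

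Assume that every missing participant was last seen at week 8.

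| Assumption | Calculation | Shift |
|---|---|---|
| 10% missing per arm; falls of 15 points (acupuncture) and 5 (control) | 0.10 × 0.15 − 0.10 × 0.05 | +1.0 point |
| Same, falls swapped | 0.10 × 0.05 − 0.10 × 0.15 | −1.0 point |
| Equal fall of 15 points; 15% v 5% missing | 0.15 × 0.15 − 0.05 × 0.15 | +1.5 points |
| Same, losses swapped | 0.05 × 0.15 − 0.15 × 0.15 | −1.5 points |
| Equal loss and equal fall | terms cancel | 0 |

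**3. Scale.** The standard error of the difference at 109 per arm is √[(0.46 × 0.54 + 0.35 × 0.65)/109] = 0.066, or 6.6 points. The shifts are 1.0/6.6 = 0.15 and 1.5/6.6 = 0.23 standard errors. Against the cited difference of 46 − 35 = 11 points, 1.0 point is 9%.

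**4. Uncertainty left out.** With 10% missing, about 11 of 109 per arm are filled and 98 observed. Treating all 109 as observed gives 6.6 points. If earlier windows carried no information on week 16, the honest figure would be near that for 98 per arm: √[(0.46 × 0.54 + 0.35 × 0.65)/98] = 0.070. The ratio is √(109/98) = 1.05, so the understatement from this source is about 5%, and less if earlier windows are informative.

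**5. The plan's own rules compared.** Take 98 observed per arm at 46% and 35%, and 11 missing per arm. The odds ratios are computed from the resulting proportions.

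| Rule for the 11 missing | Acupuncture v control | Odds ratio |
|---|---|---|
| All nonresponders | 41.4% v 31.5% | 1.54 |
| Carried forward, rates equal to observed | 46.0% v 35.0% | 1.58 |
| Carried forward, 60% (assumed) in acupuncture, 35% in control | 47.4% v 35.0% | 1.67 |
| Acupuncture nonresponders, control responders | 41.4% v 41.6% | 0.99 |
| Acupuncture responders, control nonresponders | 51.4% v 31.5% | 2.31 |

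**6. Agreement within a participant.** A simulation assumed baseline mean 22 days (SD 4, limited to 15–28), week-8 mean 12.5 (SD 6), a week-8 to week-16 correlation of 0.5, and mean worsening by week 16 of 0, 2 or 4 days. Carried-forward status disagreed with one imputed status in about 31%, 30% and 32% of missing participants. Two imputations of the same participant disagreed with each other in about 38 to 39%, 33% and 26%.

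**The case against.** **Carrying forward may not be the primary rule at all.** The Primary outcome section counts missing as nonresponse. If that rule governs, nothing is carried forward and the persistence argument falls. This stands: the two sections conflict, and that conflict matters more than the present point. But choosing the nonresponder rule would still leave the primary outcome out of step with the multiply imputed counts.

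**There may be nothing to impute.** The analysis set requires at least one assessment of the primary outcome. If that means the week-16 assessment only, nobody in the set has it missing. That reading would empty the imputation sentence of content, so the wider one, any headache-day assessment after baseline, is more sensible. The text leaves it open.

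**The direction is not known.** A reader might infer that carrying forward favours acupuncture. The documents do not support this. The Discussion cites a trial in which the acupuncture effect was maintained for 20 weeks, alongside the review in which the placebo effect fell after week 12. On that evidence carrying forward could be conservative, as the swapped row in step 2 shows.

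**The results do not contradict each other.** A reader might infer that primary and secondary results could not be reconciled. Step 6 shows that disagreement within a participant is partly inherent in imputation, since repeated draws also disagree. The results are group-level, on different scales and from different models. What remains is inconsistency of assumptions.

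**Sensitivity analyses are planned.** The two extreme cases bracket any assumption about those lost to follow-up. They expose dependence on missing data, but a range of 0.99 to 2.31 (step 5) neither confirms nor replaces the primary estimate, and none of the three applies multiple imputation to response.

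**Multiple imputation is not free of bias.** As usually run, it relies on data being missing at random, which the protocol neither states nor supports. Its advantages here are that it uses all observed windows, carries the uncertainty through and is already planned for the same diary data.

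**Conclusion.** The point holds in a limited form. The plan treats one missing diary window in two incompatible ways, and its rule for the primary outcome can carry an on-treatment response into a post-treatment endpoint and count it as observed.

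The likely effect is small: about 1 to 1.5 points in either direction, or 0.15 to 0.23 of a standard error. This rests on assumed losses of 5% to 15% per arm, assumed falls of 5 to 15 points, and a last diary at week 8 for everyone missing. Later last diaries would reduce it; larger losses would increase it. The documents give no on-treatment response rates, so neither sign nor size can be fixed.

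The number of imputations is not part of the point. Relative efficiency with five is 1/(1 + γ/5), which is 0.98, 0.96 and 0.94 at 10%, 20% and 30% missing information (γ), so using more is a minor preference.

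The case for change is that a more coherent method is already in the plan and costs little to extend.

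**What to change.** 1. Impute the 4-weekly headache-day counts once, separately by arm, using the baseline count, all observed windows and the model covariates (sex, age, duration of headache).
2. Derive both week-16 responder status and the headache-day outcome from the same imputed sets, and combine the results by Rubin's rules.
3. Keep last-observation-carried-forward, the nonresponder rule and the two extreme cases as sensitivity analyses.
4. State this single primary rule in both the Primary outcome and Statistical analysis sections, and say which assessments count towards entry to the analysis set.

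The cost is a change of wording and a little analysis work, since imputation of headache days is already planned. The primary confidence interval may become slightly wider because it would then include imputation uncertainty.

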### Participants

#### Study population and sample size

We will recruit CTTH sufferers who meet the diagnostic criteria in the International Classification of Headache Disorders, 3rd Edition (ICHD-3) formulated by the International Headache Society [1]. According to a previous study [11], the proportion of responders (at least 50% reduction in days with headache) was 46% after acupuncture treatment versus 35% after superficial acupuncture (odds ratio, 1.32). In this study, we expect an odds ratio of 1.35 when acupuncture is compared with superficial acupuncture. Assuming a significance level of 0.05, a study power of 0.8, and a correlation of 0.5 between independent variables (including study groups, assessment intervals, and the number of headache days at baseline), 199 participants are required to reject the hypothesis that acupuncture is equivalent to superficial acupuncture. Taking a 10% attrition bias into consideration, we will recruit 218 participants in total, with 109 in each group.

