A recent RCT reported that the acupuncture effect can be maintained for 20 weeks after 20 sessions of treatment over 4 weeks, which could be considered as powerful evidence for the existence of a sustained effect produced by acupuncture [43]. In addition, a systematic review indicated that the placebo effect of acupuncture showed a unique pattern according to time, which increased from baseline to 12 weeks and decreased after 12 weeks [44]. Considering the necessity of a relatively long observation period, we will conduct the trial over a period of 36 weeks and make assessments every 4 weeks, which aims to not only evaluate the long-term effect of acupuncture for CTTH, but also distinguish curative effects from placebo effects of acupuncture. However, the long observation period has its limitations. It may increase the rate of patient dropout and we will not know if the patients receive other treatments in the follow-up period. To minimize the potential bias, we formulate the plan to reduce dropout by establishing good communication relationships with participants and maintaining close contacts via telephone calls, text messages and emails during the follow-up period. Moreover, characteristics of the dropouts will be extracted and analyzed, which can help judge whether the results are affected by the bias.

In conclusion, the results of this trial are expected to not only provide clinical evidence of the effectiveness of acupuncture as a painkiller, but also evaluate the duration and intensity of the acupuncture effect for CTTH.

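### The protocol fixes only 5 imputations for missing secondary values: valid, but needlessly noisy for borderline results, and free to improve

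*Protocol article*

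**What the plan says.** The Statistical analysis section states: "Missing values in the secondary outcomes will be imputed by using the multiple imputation method", and gives n = 5 in parentheses. I read n as the number of imputed data sets, which is the natural meaning. No secondary outcome is excepted and no reason is given for the number.

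The same section handles the primary outcome separately, by carrying the last observation forward, with three sensitivity analyses that count those lost to follow-up as responders or nonresponders. It also says that "all statistical hypotheses will be two-sided tests".

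On the expected amount of missing data, the section Study population and sample size says: "Taking a 10% attrition bias into consideration, we will recruit 218 participants in total, with 109 in each group". The Discussion says of the long observation period: "It may increase the rate of patient dropout". It gives no figure, and it goes on to describe contact with participants meant to limit losses and an analysis of those who drop out.

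**The concern.** A multiple-imputation estimate is an average over randomly drawn data sets. With few draws, that average, its standard error and its p-value change when the analysis is rerun with another seed. If the change is large relative to the standard error, a result near 0.05 can fall on either side of it by chance of the seed.

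This has some weight here because the primary outcome is a single binary measure at week 16. What the trial says about how long and how strongly the effect lasts will draw on secondary outcomes followed to week 32, over a period in which the protocol itself expects that dropout may rise. The number is also a setting that the protocol states, so this is not a detail left to a separate analysis plan.

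**Working it through.** **Inputs from the protocol article.** Number of imputations m = 5 and two-sided tests (Statistical analysis); significance level 0.05, power 0.80, 10% attrition, 199 participants needed and 218 recruited (Study population and sample size). The figure m = 5 is a chosen setting without a derivation, so there is no calculation of the plan's to reproduce.

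**Assumption.** FMI is not in the documents. I take 10%, equal to the planned attrition, and show 5% to 30%.

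**Step 1: noise in the pooled estimate.** Its Monte Carlo standard deviation, in standard-error units, is sqrt(FMI/m). With m = 5 and FMI 10%: sqrt(0.10/5) = 0.14. At 5%, 20% and 30% it is 0.10, 0.20 and 0.24. With m = 50 and FMI 10%: sqrt(0.10/50) = 0.045.

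**Step 2: efficiency.** Relative efficiency is 1/(1 + FMI/m). With m = 5 and FMI 10%: 1/(1 + 0.02) = 0.98. At 5%, 20% and 30% it is 0.99, 0.96 and 0.94. The loss is therefore about 2%, with a range of 1% to 6%.

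**Step 3: a hand check on p-values.** Take a result at z = 2.0 and FMI 10%. With m = 5, the 95% range of z over seeds is 2.0 ± 1.96 × 0.1414 = 1.723 to 2.277, which is p = 0.085 to 0.023. With m = 50 it is 2.0 ± 1.96 × 0.0447 = 1.912 to 2.088, which is p = 0.056 to 0.037. This step varies the estimate only.

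**Step 4: simulation with full pooling.** Rubin's rules with Barnard-Rubin degrees of freedom (complete-data value set at 195, close to the 199 evaluable participants) and 100,000 seeds per setting also bring in the noise in the standard error. For a result whose p-value with very many imputations is 0.04, the share of seeds giving p of 0.05 or more is:

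| Assumed FMI | m = 5 | m = 20 | m = 50 | m = 100 |
|---|---|---|---|---|
| 5% | 22% | 4% | 0.3% | below 0.1% |
| 10% | 34% | 13% | 3% | 0.3% |
| 20% | 44% | 25% | 12% | 4% |
| 30% | 49% | 33% | 20% | 10% |

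At FMI 10% the 95% seed range of that p-value is 0.019 to 0.089 with m = 5 and 0.032 to 0.051 with m = 50. In the other direction, a result with a limiting p of 0.06 falls below 0.05 in 26% of seeds with m = 5 and 4.5% with m = 50.

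**Step 5: without conditioning on a borderline result.** Type I error with m = 5 stays at about 0.05 throughout. For a comparison with nominal 80% power and FMI 10%, power is 78% with m = 5 and 79% with m = 100. Two seeds disagree on significance in 5.7% of such trials with m = 5 (3.5% at FMI 5%, 13.9% at FMI 30%) and in 1.6% with m = 50 (1.0% to 3.2%).

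**The case against.** The strongest reply is that nothing is invalid. Rubin's rules already add the between-imputation variance divided by m and adjust the degrees of freedom, so the noise from a finite m is inside the reported interval. Steps 2 and 5 bear this out, with type I error at its nominal level and an efficiency loss near 2% at the planned attrition. The 34% also applies only to a result already close to 0.05; over all trials, seeds disagree much less often. Repeated 4-weekly measurements on the same participant may predict the missing values well, so an FMI below 10% is plausible. And no decision rule hangs on a single secondary p-value. All of this stands, and it is why the point is minor.

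Two stronger readings should be set aside. A reader might infer that every secondary result depends on five imputations. Only missing values are imputed, and with 10% attrition roughly 90% of values would be observed. A reader might also infer from the Discussion that most data from the later visits will be missing. The protocol says only that dropout may increase, and it sets out steps against this.

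What the reply does not remove is that the noise is avoidable. Validity on average over seeds does not make one reported borderline result reproducible.

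**Conclusion.** The point holds as a free improvement of low severity. Five imputations give valid inference for the incomplete secondary outcomes but leave a reproducibility problem for results near 0.05, and step 4 shows that it is already visible at the planned attrition. Every seed figure rests on the assumed FMI, and the share that crosses 0.05 also rests on the result being borderline. The documents do not support a claim of bias, of inflated type I error, or of any effect on the week-16 responder analysis.

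**What to change.** In the Statistical analysis section, replace 5 with at least 50 imputations for the incomplete secondary outcomes. Twenty is not quite enough: at FMI 10% it still leaves about 13% of seeds crossing 0.05 in the example above. Fifty brings this to about 3%. If missingness turns out well above plan, a larger number is worth using, since at FMI 20% the share is 12% with 50 and 4% with 100. The estimand, model, visits and participant burden do not change. The only cost is computing time.

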## Discussion

Previous RCTs have been conducted to explore the effect of acupuncture for TTH compared with no treatment [11, 23], sham interventions (non-skin-penetrating techniques or needling non-acupoints) [9, 11–13, 16], or other treatment (relaxation, massage, or physiotherapy) [17, 26–28], but the conclusions remain controversial. In a recent Cochrane systematic review [15], seven of the 12 included trials recruited both episodic and chronic TTH patients [9, 11, 13, 23–26, 28], which made it relatively difficult to evaluate the effect of acupuncture for CTTH separately and precisely. Three of the 12 trials [16, 17, 27] included participants with CTTH only, but their small sample sizes, various types of acupuncture interventions, non-uniformed comparisons, and different observation periods may lead to an uncertain evaluation of acupuncture effect. Therefore, we designed a two-armed, parallel-design, patient-assessor blind, RCT to explore and evaluate the long-term effect of acupuncture for CTTH treatment. In this trial, we will compare acupuncture with superficial acupuncture to clarify the long-term therapeutic effect of acupuncture for CTTH.

In this trial, participants in different groups will receive treatments in different rooms to block the communication between the two groups and reduce patients’ doubts about different interventions. Moreover, all of the acupuncture manipulations will be performed on the fixed main acupoints by two trained acupuncturists who have passed the special training examination, in order to reduce the influence of participants’ psychological factors on clinical effects. It is reported that negative mood state has a close relationship with TTH [29, 30] Therefore, psychological assessments of participants based on HAMA and HAMD are planned. Furthermore, we will pay special attention to the recording of the *deqi* sensation, which may enhance the acupuncture effect as described in TCM classical works and traditional acupuncture theory [31].

A placebo control plays a crucial part in evaluating the effectiveness of a treatment, which can help separate the specific and nonspecific effects and reduce bias by enabling blinding. Therefore, being inert and indistinguishable from the true intervention are the main characteristics of a perfect placebo or a sham intervention. However, to devise or find adequate placebos seems too difficult for physical interventions, such as acupuncture. Currently, superficial acupuncture is considered as a type of sham acupuncture, because the needle depth does not reach acupoints’ anatomical layers. However, there is increasing evidence that sham acupuncture might be associated with larger placebo effects than pharmacological placebos [32–34], especially for some subjective outcomes and the treatment of pain [35]. A positive expectation of an intervention is an important part of the placebo effect [36, 37], which is also supported by many previous trials [38–41]. In addition, a good doctor-patient relationship also contributes to patients’ expectations, which may increase placebo effects after repeated treatments and harmonious communications [42]. It may be the reason why no significant differences of effects between acupuncture and sham acupuncture were reported by several trials [11–13, 24]. Hence, we will make a comparison of participants’ expectations between two groups to eliminate the impact on our results.

A recent RCT reported that the acupuncture effect can be maintained for 20 weeks after 20 sessions of treatment over 4 weeks, which could be considered as powerful evidence for the existence of a sustained effect produced by acupuncture [43]. In addition, a systematic review indicated that the placebo effect of acupuncture showed a unique pattern according to time, which increased from baseline to 12 weeks and decreased after 12 weeks [44]. Considering the necessity of a relatively long observation period, we will conduct the trial over a period of 36 weeks and make assessments every 4 weeks, which aims to not only evaluate the long-term effect of acupuncture for CTTH, but also distinguish curative effects from placebo effects of acupuncture. However, the long observation period has its limitations. It may increase the rate of patient dropout and we will not know if the patients receive other treatments in the follow-up period. To minimize the potential bias, we formulate the plan to reduce dropout by establishing good communication relationships with participants and maintaining close contacts via telephone calls, text messages and emails during the follow-up period. Moreover, characteristics of the dropouts will be extracted and analyzed, which can help judge whether the results are affected by the bias.

In conclusion, the results of this trial are expected to not only provide clinical evidence of the effectiveness of acupuncture as a painkiller, but also evaluate the duration and intensity of the acupuncture effect for CTTH.

